## Specific Objectives

**Primary objectives:**

- Determine the effectiveness of the *WHO Package of Essential Non-communicable Disease interventions for primary health care in low resource settings* (WHO PEN), integrated with standard of care HIV management guidelines, in identifying and in modifying risk factors for atherosclerotic cardiovascular disease in women receiving HIV care.
- Compare cardiovascular disease (CVD) risk scores using the WHO PEN *WHO/ISH Cardiovascular risk prediction chart for WHO epidemiological sub region AFR E*, *Data collection on adverse effects of anti-HIV drugs study (DAD risk assessment) and Framingham risk assessment* with short-term cardiovascular disease outcomes (presence of subclinical atherosclerosis by means of CMIT, presence of CVA, Myocardial infarction, Angina) in women aged over 40 years.

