# research design and methods

## Overview

1. Study Setting: Umlazi/Philasande Research Clinic and Gateway Umlazi Clinic
2. Study Design: This study is a prospective two-arm, quasi-experimental design comparing a primary health care intervention plan with usual care.
3. Target Population: HIV infected women attending PHC
4. Study population: HIV infected women aged from 18 to 49 years of age and receiving HIV care at PHC clinics.
5. Inclusion criteria

- HIV infected women
- On ART for at least 1 year
- Equal to/older than 18 years of age
- Equal to/younger than 49 years of age
- Plans to remain in the study catchment area for at least 3 years

1. Exclusion criteria

- Participant declines study participation

1. Sampling

• Size of sample

400 HIV-infected women consisting of an intervention arm of 200 women co-enrolled in the PROMOTE study at the Umlazi CRS (see method of sampling for details), and a control arm of 200 women receiving HIV care at the PHC. With a 20-30% estimated prevalence of metabolic syndrome in people living with HIV without any specific intervention in the risk factor modification of cardiovascular disease and a proposed 10-15% estimated incidence of metabolic syndrome in the intervention arm, 132 participants per arm would allow for 80% power. An additional 10% can be added to allow for loss to follow-up. The larger proposed sample size will allow for external validity / generalizability.

- Method of selecting sample

Two HIV-infected female cohorts will be matched for receipt of ART duration >1 year and for age will be compared in the study. Method of selection will be via convenience sampling.

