**Intervention group**: There are 245 HIV infected women between 18 and 49 years of age, who have been on ART for more than 1 year and attending the CAPRISA Research Clinic in Umlazi. These women were enrolled into the PEPFAR PROMise Ongoing Treatment Evaluation (PROMOTE) observational study from May-June 2017. This study has been implemented to provide long-term follow-up data on safety outcomes of widespread use of combination antiretrovirals (cART) among an already well-characterized cohort of HIV infected mothers and their children who previously enrolled in the multi-site PROMISE study. This cohort was selected for the proposed intervention arm because the principal investigator is based at the research clinic. Women will be briefed at their next PROMOTE study visit and the 1^st^ 200 interested candidates meeting all eligibility criteria will be co-enrolled into the Intervention arm of the Sub-study.

**Control group**: The Tier data base will be used to select HIV infected women aged between 18-49 years, receiving ART for more than 1 year at the Umlazi Gateway PHC. Scheduled clinic visits at similar time points to the anticipated clinic visits in the intervention group will be used to establish a list of potentially eligible women. Following a matched pool of data, the first 200 women fulfilling the inclusion criteria, who attend the clinic for their next appointment and who consent to study participation will be enrolled.

1. Data sources

- Intervention group: Each participant in the intervention group will be assigned a new Participant identifier number (PID) in addition to the PROMOTE PID. History taking and physical exam, as well as laboratory results and where applicable ultrasound reports, will be entered directly into a data collection tool on a Microsoft Excel spreadsheet (Appendix I).
- Control group: Participants will be assigned a PID in addition to their clinic chart number. Information from clinic patient medical records will be entered directly into the data collection tool (Appendix II). At the final study visit; history, physical exam, lab report finding and ultrasound findings (where applicable), will be source documented.

1. Measures to ensure validity

- Internal
- The prospective nature of the study, large sample size, careful matching between cohorts by age category and by duration of ART aims to counteract the potential for selection bias.

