- **Intervention group**: The prevalence of CVD risk factors will be determined by data collection through history taking, physical examination, and laboratory and radiology investigations as per the data collection tool. CVD risk assessment will be performed annually using a combination of the WHO and International Society of Hypertension cardiovascular risk prediction (WHO/ISH) and the DAD CHD equation. The intervention proposed is a modified WHO PEN algorithm incorporated into HIV management guidelines at study entry. Trends in all risk factors will be monitored, and new risk factors identified, with 6 monthly intervention during the first year, and annually for three years thereafter.
- **Control group**: Following informed consent, data will be collected from the participants ARV clinic medical chart as per the data collection tool. Standard of care HIV management and primary health care will be provided by public sector clinic staff according to current national guidelines. No study investigations or study questionnaires will be carried out at entry visit until the final study visit. There will be regular telephonic follow up with the participants to maintain study retention. Chart review data collection at 6 monthly intervals. CVD risk factors, as per outcomes described above, will be measured by the study at a single 3 year final study visit. Information obtained will be conveyed to the clinic staff for further management if required.

1. Plan for Data handling/processing

- Data will be analysed using SAS or SPSS software

1. Statistical methods

- Descriptive statistics-continuous variables will be represented by means, medians, prevalence, standard deviation.

The categorical variables will be represented by N+%

- Analytic statistics

The continuous variables will be compared by use of t-tests or Wilcoxon rank sum tests.

The categorical variables will be compared using Chi sq or Fisher’s exact test/

- Logistic regression will be applied to identify predictors of cardiovascular disease between the two arms, and between those participants who exhibit atherosclerosis by carotid intima thickness and those who don’t.

1. List of possible confounders

- Women in the intervention group are already enrolled in a study with controlled settings. These women may have commenced ART with a higher baseline CD4 counts.
- Multivariate logression analyses will be utilized in order to control for confounders.

1. List of associations to be measured

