|  | BMI | WC | Fasting lipogram | Systolic BP | Fasting  Glucose | Urine microalbumin | hsCRP | Carotid initima medial thickness |
| --- | --- | --- | --- | --- | --- | --- | --- | --- |
| Age | x | x | x | x | x | X | x | X |
| Family History  of CVD | x | x | x | x | x | X | x | X |
| Tobacco use | x | x | x | x | x | X | x | X |
| Diet | x | x | x | x | x | X | x | X |
| Exercise | x | x | x | x | x | X | x | X |
| ART regimen | x | x | x | x | x | X | x | X |
| ART duration | x | x | x | x | x | X | x | X |
| VL | x | x | x | x | x | X | x | X |
| CD4 | x | x | x | x | x | X | x | X |
| BMI |  |  | x | x | X | X | x | X |
| WC |  |  | x | x | X | X | x | X |
| Fasting Lipogram |  |  |  | x | X | X | x | X |
| Systolic BP |  |  |  |  | X | X | x | X |
| Fasting Glucose |  |  |  |  |  | X | x | X |
| U-microalbumin |  |  |  |  |  |  | x | X |
| hsCRP |  |  |  |  |  |  |  | X |
| CVD risk % by Framingham |  |  |  |  |  |  |  | X |
| CVD risk % by DAD |  |  |  |  |  |  |  | X |
| CVD risk % by WHO/ISH |  |  |  |  |  |  |  | X |

1. Calculate cardiovascular risk as per WHO –ISH, DAD and Framingham, annually in intervention group and in the control group at year 3 and compare short term outcomes (presence of subclinical atherosclerosis by means of CMIT, presence of stroke, MI, angina -ischaemic heart disease)

1. Intervention:

**DIETARY CHANGES:** All individuals encouraged to reduce daily salt intake by at least one third and, if possible, to <5 g per day, to eat at least 400 g a day of a range of fruits and vegetables as well as whole grains and pulses and to reduce total fat and saturated fat intake

**PHYSICAL ACTIVITY:** All individuals encourage to do at least 30 minutes of moderate physical activity (e.g. brisk walking) a day, through leisure time, daily tasks and work-related physical activity.

**WEIGHT CONTROL:** All individuals who are overweight or obese should be encouraged to lose weight through a combination of a reduced-energy diet and increased physical activity

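### In the clinical-event part of primary objective 2, new stroke, MI and angina are not separated from earlier disease, and in controls every counted event precedes or coincides with the only risk score

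*Protocol*

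**What the plan says.** Under Specific Objectives, the second primary objective compares three risk scores with short-term outcomes. These are subclinical atherosclerosis by CIMT and "presence of CVA, Myocardial infarction, Angina) in women aged over 40 years". The methods (Overview, item on calculating cardiovascular risk) repeat the clinical outcomes as "presence of stroke, MI, angina -ischaemic heart disease". Neither place gives an onset window or restricts the outcome to events after entry.

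The only exclusion criterion is "Participant declines study participation", so a woman with an earlier stroke, MI or angina may enrol in either arm.

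Score timing differs by arm: every year in the intervention arm, but "in the control group at year 3 and compare short term outcomes". For controls, the plan for data collection states: "No study investigations or study questionnaires will be carried out at entry visit until the final study visit". The data sources item adds: "At the final study visit; history, physical exam, lab report finding and ultrasound findings (where applicable), will be source documented". Before that visit, control data come from six-monthly chart review. The schedule of evaluations places CIMT at year 3 only, in women over 40.

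The literature review (CVD risk assessment tools in HIV) describes DAD as an absolute 5-year risk and WHO/ISH as a 10-year risk, with WHO/ISH assessment starting at age 40.

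**The concern.** A risk score is meant to be computed before the outcome in people who have not yet had it. If a woman has already had a stroke or MI, her later score may use values changed by it, such as treated blood pressure or a changed smoking status. The bias can run either way. Treated survivors can look low-risk, and old disease can look as if the score had predicted it.

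Objective 2 is primary. If its event results were reported as evidence of how well the scores perform, the control arm would contribute associations with past disease only. In both arms, events from before entry could be counted as short-term outcomes.

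**Working it through.** **No figure to reproduce.** The protocol states no sample size or event count for objective 2. Its 132 per arm concerns metabolic syndrome and does not bear on this point.

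**Step 1. Order of measurements.**

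| | Intervention | Control |
|---|---|---|
| First score | year 1, taken here as month 0 | month 36 |
| Study-taken history | from entry | month 36 (chart review before that) |
| CIMT | month 36 | month 36 |
| Follow-up after first score | 36 − 0 = 36 months | 36 − 36 = 0 months |
| Share of DAD horizon (60 months) | 36/60 = 60% | 0% |
| Share of WHO/ISH horizon (120 months) | 36/120 = 30% | 0% |

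Month 0 is an assumption: the schedule groups months 0 and 6 as year 1 and says only that scoring is annual. In controls, no counted event can follow the score. CIMT is concurrent with the year-3 score in both arms.

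**Step 2. Can an earlier control score be rebuilt?** The protocol lists the WHO/ISH inputs as age, gender, systolic blood pressure, diabetes, total cholesterol and tobacco use. The control chart-review column of the schedule has age, systolic blood pressure and lipogram. It has no smoking entry and no fasting glucose before the final visit. As scheduled, the inputs are incomplete.

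**Step 3. How many prior and new events?** The documents give no age distribution or event rates, so all rates here are assumptions. Take 10% to 50% of 200 women per arm as over 40, that is 20 to 100 women.

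- Prior events, prevalence 0.5% to 2%: 20 × 0.005 = 0.1 to 100 × 0.02 = 2 per arm.
- New events over 3 years, lower scenario (0.1% to 0.5% per year): 20 × 3 × 0.001 = 0.06 to 100 × 3 × 0.005 = 1.5 per arm.
- New events over 3 years, higher scenario (10-year risk 5% to 20%): the 3-year risk is 1 − (1 − r)^0.3, which is 1.53% at r = 5% and 6.48% at r = 20%. This gives 20 × 0.0153 = 0.3 to 100 × 0.0648 = 6.5 per arm.

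The ratio of prior to new events does not depend on the number of women:

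- Lower scenario: 0.005/0.015 = 0.33 to 0.02/0.003 = 6.7.
- Higher scenario: 0.005/0.0648 = 0.08 to 0.02/0.0153 = 1.3.

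Prior events may be a small part of the count or most of it. The total is small in every case.

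**Step 4. Comparison with CIMT.** The literature review cites a 12% prevalence of subclinical atherosclerosis in a local, mainly female cohort. Set against an assumed 3-year event risk of 0.3% to 6.5%, CIMT would supply more outcomes than new events for any number of women.

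**The case against.** The strongest reply is that the protocol only says the scores are compared with outcomes and does not promise predictive validation. The association grid pairs the three scores with CIMT alone, and the planned logistic regression contrasts women with and without atherosclerosis by CIMT. For CIMT, a year-3 score is a coherent cross-sectional comparison. This stands, and it confines the point to clinical events. For those events the reply does not hold, because forward risk scores set beside outcomes labelled short-term invite a predictive reading. Even read as cross-sectional, undated events would not be short-term outcomes.

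A second reply is that an analysis plan can settle the details. It can restrict the analysis to new events, but it cannot supply a control score that the schedule does not collect.

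Four stronger readings are tempting but unsupported:

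- **The arms are pooled, mixing opposite time orders.** The protocol does not say so; it states score timing by arm and leaves the handling open.
- **Nothing is known of a control's history before month 36.** Chart data are collected from consent onwards. The data collection tools are not shown in the copy read, so the absence of an event or date field cannot be established. An event found in the chart would still not come after the only score.
- **Lifetime events are certainly counted.** The label short-term leaves this ambiguous. The fault is that the text does not rule them out.
- **Objective 2 as a whole fails.** The CIMT part remains usable.

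**Conclusion.** The point holds for the clinical-event part of primary objective 2 and should be corrected. Prior disease is neither excluded nor separated from new events in either arm. In controls, follow-up after the score is 0 months, so the comparison cannot show how forward risk scores relate to later events. The control timing follows from the protocol's own schedule and needs no assumption.

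The numerical effect does rest on assumptions. With 20 to 100 women over 40 per arm and the rates above, prior events would number 0.08 to 6.7 times the new ones, with at most about 6.5 new events per arm. So few events support description and little inference, however they are classified. This limits the consequence to how the event results are worded and interpreted.

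**What to change.** - Define the event outcome as first stroke, MI or angina after entry, with the date taken from chart or history. Leave women with earlier events out of this analysis.
- Relate new events to the month-0 score in the intervention arm only, and state that the first annual score is taken at month 0. Use WHO/ISH only for women aged 40 or over at month 0, since a woman aged 37 to 39 at entry can reach 40 during the study without having a valid entry score.
- Report control-arm events descriptively, with no predictive claim.
- Present year-3 score versus CIMT as a cross-sectional association by arm, with month-0 score versus CIMT in the intervention arm as the only prospective CIMT analysis.

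The cost is a rewording of objective 2 and its analysis, plus an event-date field if the tools lack one. Fewer women enter the prospective comparison, controls leave the event analysis of a primary objective, and the claim is weaker. The intervention also targets factors that enter the scores, so the prospective result describes the scores under active risk modification and should be reported as such.

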# Ethical Considerations

- Permissions needed to conduct the study will be obtained from the University of KwaZulu- Natal Biomedical Research Ethics Committee, Prince Mshiyeni Memorial Hospital, KwaZulu-Natal Department of Health and the PROMOTE protocol team.
- Written informed consent form will be obtained prior to any study procedure.
- All study procedures will be conducted in a manner to protect participant privacy and confidentiality.
- There will be no additional reimbursement in the intervention arm of the proposed sub study. Participants enrolled in the PROMOTE study are reimbursed using PROMOTE funds. There will be no reimbursement in the control arm with the exception of the final study visit, during which additional lab assessments will be carried out during their routine PHC visit. .

#

## Appendices Data Collection Tool – Intervention

[figure not shown]

## Data Collection Tool – Control

[figure not shown]

Supplement: S1 File — (DOCX) [file pone.0255652.s001.docx]
